##### Psychosocial functioning

###### Interpersonal problems

The Inventory of Interpersonal Problems (IIP; [108]) is a self-report measure of problems in interpersonal relationships. It is widely used in psychotherapy research.

###### Interpersonal trust

Primal trust in a helping Other has been proposed as an important feature of therapeutic interaction [47]. We will use the Trust game to measure trust and reciprocity in participants [109]. This is a paradigm drawn from behavioral economics that tests how much money a person would give to a stranger in order to potentially receive a higher amount [110].

###### Therapeutic Alliance

Alliance plays an important role in effective psychotherapy [111]. Alliance with the individual therapist will be assessed using the patient self-rated Working Alliance Inventory Short-Form (WAI-SR; [112]).

###### The Global Assessment of Functioning (GAF)

Is a numeric scale (0 through 100) used by an independent coder to rate the social, occupational and psychological level of functioning [113]*.*

###### Work Ability Index (WAI-SR)

A previous study found that short- and long-term psychodynamic psychotherapy were differentially effective in improving work ability [114]. We will use the WAI to assess work ability, a questionnaire used in occupation health and research [115].

###### MRI Scanning MR spectroscopy (1H MRS)

Scans are acquired on 3.0 T scanners, Siemens Prisma in Frankfurt subgroup only. Spectroscopy was performed at the end of the MRI examination. An axial slice was recorded with 2D MRSI using an acquisition weighted circular phase encoding scheme on a 20 × 20 matrix, FOV of 240 × 240 mm^2^, 12 mm slice thickness, nominal voxel size of 12 × 12x12 mm^3^, TR 2000 ms, TE 40 ms, and 2 acquisitions. The volume of interest (VOI), which was selected by using the sLASER sequence from the vendor and outer volume suppression, was adjusted to contain GM and WM. Spectra were analyzed using LCModel [116]. The basis data set contained simulated spectra from Alanine, Creatine, GABA, Glucose, Glutamine, Glutamate, Glycine, Choline, Glutathion, Lactate, Mio-Inositol, N-acetyl-aspapartate-glutamate and N-Acetyl-Aspapartate.

## Procedures

### Data collection sites

Recruitment and treatment sites will be located in one center in the US (Los Angeles) and six centers in Europe (Germany: Frankfurt a.M., Cologne, Leipzig, Giessen, Mainz; and Switzerland: Lausanne). MRI scanning occurs in Los Angeles, Frankfurt a.M., and Lausanne. MRI data are processed in Los Angeles (CHLA). A clinical agreement has been signed and approved by each participating site.

### Patient recruitment

Patients will be recruited in private psychotherapeutic and psychiatric practices, in outpatient clinics for mood disorders in hospitals. Patient flyers describing study aims and procedures will be available to potential participants with a likely diagnosis of chronic depression. Healthy controls will be recruited through informal networks. Patients with a likely diagnosis of chronic depression (BDI-II > 17) and interested healthy volunteers will be referred to the respective study center in each country and thereafter interviewed for eligibility by a research assistant.

### Presentation of the study and informed consent procedures

The study will be presented to potential participants. Documents explaining the study, with its aims, procedures, benefits and risks for the participants will be provided to the participants. Interested subjects will be given a period to consider whether they would like to participate and the research team will be at their disposal to answer their eventual questions on their participation. Subjects confirming their interest in participating will then be asked to provide their informed consent to be randomly assigned to one of the treatment settings, to participate in the diagnostic, MRI, and psychometric procedures, to agree that some psychotherapy sessions are audio recorded, and agree to participate in the follow-up measurements). Participants with chronic depression and early life trauma will then be randomized in one of the two intervention groups.

### Randomization

The randomization procedure will consist of a computer-generated sequence of random numbers using SPSS (SPSS Statistics, version 28), which will then be used to allocate patients to either of the 2 treatment arms. The randomization sequence will be generated and maintained by an independent study administrator in Frankfurt. Once the patient is included the ID number is communicated to the study administration in Frankfurt. On the same day, the randomization arm will be communicated to the local team and applied to the participant included.

### Blinding

All the members of the investigating team (SCID /LIFE interviewers, MRI team etc.) will be blinded (they do neither know the treatment arm nor the names of the study therapists).

### Rater training

SCID interviewers will be masters-level psychologists, previously trained on administration of SCID and supervised be a senior study investigators.

### Manualized psychotherapeutic interventions

In the LAC study, therapists were trained in the specific treatment technique of psychoanalysis using the Tavistock Manual [117, 118], which we have modified and extended for the MODE study [119]. The MODE manual was developed by leading clinical experts of all participating sites of the study. It integrates various psychoanalytic traditions and cultures for treating chronically depressed, traumatized patients and describes high- and low-treatments. French and English translations are available.

### Therapist selection and training

Both interventions will be delivered by board certified psychoanalytic therapists which have trainings and clinical experiences in low frequent and high frequent psychoanalytic therapies. Trained therapists will deliver both treatments, depending on their availability and vacancies at the time of participant enrollment. All MODE therapists are trained in the Manual [119]. Most of the study therapists in Germany have already been trained and worked in the LAC Study. Additional training will be offered for them and the new MODE study therapists of all centers in several workshops. It will include theoretical presentations, group discussion of exemplary cases, and individual case presentations. Training will be conducted by expert trainers who are qualified psychoanalysts and authors or collaborators in developing the Manual.

### Clinical supervision

All study therapists will participate in monthly group supervisions or in one of the monthly “Clinical Conferences” (chairs in Germany: [name], [name], in Lausanne: [name], in SF/LA: [name]), where therapists present their ongoing psychoanalyses with study patients.

### Recording and transcription

A random selection of therapy sessions will be audiotaped. Adherence to the treatment protocol will be assessed by independent members of the research teams using the Comparative Psychotherapy Process Scale (CPPS; [120], see also [29]).

### Power calculation

Power analyses using MRI measures from prior RCTs of medication therapy for the treatment of chronic depression [81, 82] indicated that a sample size of N = 30 participants for each of the 3 arms of the study would afford us a power of 80% to detect a moderate-to-large effect size (Cohen d = 0.5) with an α = 0.05 in each imaging modality (anatomical, task-based fMRI, resting state fMRI, and DTI).

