## Methods/Design

### Study design

MODE is a randomized, parallel, superiority and single blinded controlled trial comparing the effectiveness of two active interventions – high frequency (*n* = 30) vs low frequency (*n* = 30) psychoanalyses – in modifying brain structure and function over one year of treatment chronic depression patients who have a history of early life trauma (Fig. 1).

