**Fig. 1 Fig1:**
[figure not shown]
Flow chart of the study

This study design will overcome many of the limitations of prior psychotherapy effectiveness studies. It will include an active control condition rather than a mere wait list, thereby controlling for the effects of interpersonal attention and interaction. Randomization and statistical evaluation will be performed by independent teams. Moreover, the active comparator condition, low frequency psychoanalysis, will help to control for the “allegiance” effects that confound most psychotherapy trials [85]. Finally, comparing high vs low frequency psychoanalyses will inherently provide an assessment of dose–response effects of psychoanalytic therapy on brain structure and function. Establishing dose–response associations will further improve causal inference in our study design.

In addition to randomization of depressed patients, we will include a group of healthy control participants (*n* = 30) who are free of psychiatric illness. They will not undergo treatment and therefore will not be randomized. They will undergo similar assessments and MRI scanning at one-year intervals. Their measures will serve as reference points to help discern whether study treatments induce brain changes toward or away from normal values.

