### Intervention and comparator

Study intervention will be comprised of low frequency psychoanalytic psychotherapy (1 session a week) for early traumatized, chronically depressed patients and high frequency psychoanalytic psychotherapy (3–4 weekly sessions). The active comparator condition, low frequency psychoanalysis, delivered by study therapists who are experts in delivering both frequencies, and with the same overall manual based theoretical framework and technical interventions [86], will ensure that they will be equally aligned to both high and low frequency therapies. A group of healthy controls will be needed for brain imaging comparison purposes. A control group will allow to measure cortical thickness in patients with chronic depression in comparison to healthy control participants. Therapy sessions (45–50’ each) will be delivered in the private practice rooms or rooms of the outpatient clinics of the local psychotherapeutic institutions. Patients who will require a combination therapy of medication and psychotherapy during treatment will not be excluded but form a special subgroup that will be treated separately during data analyses. Patients who will require a change in psychotherapy setting during treatment according to patient and therapist decision will be analyzed as randomized. MODE study duration will be one year, but after 1 year of treatment initiation, treatment may continue according to patient and therapist decision. Treatments will be financed in the usual way in the participating countries (in Germany by the health insurance companies, in the US and Switzerland partly by the health insurance companies, partly by the patients themselves).

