### Data analysis

Analyses will follow an intent-to-treat strategy comparing patients in the groups to which they were originally randomized.

All data will be scored and rescored by separate staff members and checked for accuracy prior to double entry into a REDCap database. Before conducting inferential statistics, we will explore data using descriptive analyses, data visualization, and examining the distributions of all imaging and clinical data. When necessary for continuous variables used as dependent variables, appropriate transformations to obtain approximate normality will be performed.

We will test a priori Primary Hypotheses in the 60 depressed participants by assessing a treatment-by-time interaction in multiple general linear models with repeated measures analyses in an intent-to-treat analysis applied to our various brain measures as dependent variables, including cortical thickness, task-based fMRI activation, resting state connectivity, and FA & ADC measures. Treatment (high vs low frequency) will be the independent variable. When testing hypotheses, we will account appropriately for the correlation of repeated measures across the two time points of measurement (baseline and 1 year) and the spatial correlation within each of our imaging measures. Covariates will include age and sex of the participants. We will examine parameter estimates and 95% confidence intervals, approximate the p-values of component terms, and estimate effect sizes in our final models. Least squares estimates (or maximum likelihood estimates) and their standard errors will be calculated for all models and plotted to assist in interpretation of significant main effects and their interactions. We will ensure that overall, study-wide Type I error-rate is maintained, correcting for multiple comparisons using False Discovery Rate (FDR). FDR-corrected *p*-values < 0.05 will be color-coded and displayed on a template brain.

The 30 healthy controls will be used to estimate the mean and variance of brain measures in the healthy population quantify the effects of high and low frequency psychoanalysis on brain measures and to aid their interpretation as either normalizing a previously abnormal brain measure or introducing a new brain difference that attenuates symptoms.

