#### Missing data

We will model missing responses/covariates in our longitudinal models. We will consider missing data mechanisms, including missing completely at random, missing at random, or missing not at random, to handle missing data due to a missed assessment time point, study dropout, or unusable MRIs. The full information maximum likelihood estimation (FIML) method will be used in fitting statistical models including LMM and LVM, which allow incomplete data (i.e., cases with missing data will contribute to the analysis).

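### The 80% power figure is tied to 30 participants per arm, which is also the full number randomised, so it leaves no visible margin for the scan loss the plan foresees and is best read as an upper limit

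*Protocol article*

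**What the plan says.** All of this is in the protocol article.

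- **Power calculation.** The text says "a sample size of N = 30 participants for each of the 3 arms of the study would afford us a power of 80" per cent, "to detect a moderate-to-large effect size (Cohen d = 0.5) with an α = 0.05 in each imaging modality". It does not name the test, the sidedness, the correlation between the two scans or a loss rate.
- **Study design.** The randomised comparison is "high frequency (*n* = 30) vs low frequency (*n* = 30) psychoanalyses". The third group of 30 consists of healthy controls, who are not randomised ("we will include a group of healthy control participants (*n* = 30) who are free of psychiatric illness").
- **Data analysis.** The primary test uses all randomised patients and no others: "We will test a priori Primary Hypotheses in the 60 depressed participants by assessing a treatment-by-time interaction". Repeated measurement is limited to "the two time points of measurement (baseline and 1 year"; Table 3 likewise shows no intermediate scan.
- **Missing data.** Missing-data mechanisms will be considered "to handle missing data due to a missed assessment time point, study dropout, or unusable MRIs". Models will be fitted by FIML, so that incomplete cases stay in.
- **Intervention and comparator.** "Patients who will require a change in psychotherapy setting during treatment according to patient and therapist decision will be analyzed as randomized".

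**The concern.** The number that carries the power claim and the number randomised are the same, 30 per arm and 60 in total. A figure of 80% for that number can describe the trial only if every randomised patient yields a usable baseline scan and a usable 1-year scan. The same article names three ways in which scans may be lost. It also allows patients to change treatment setting during the year, which can narrow the difference between the arms.

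The primary outcomes are especially exposed because there are only two scans. With several intermediate measurements, a patient who missed the last one would still inform the slope. Here such a patient informs the baseline mean and little else. The claim is also made separately for each of four imaging modalities, so a scan that fails in one modality reduces the number for that modality.

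What is at stake is how a null result would be read. If high and low frequency do not differ, readers will weigh that result as coming from a trial with 80% power for the stated effect, when the data actually available would support less.

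**Working it through.** **Inputs from the article.** 30 randomised per arm; two scans (baseline and 1 year); two randomised groups in the primary contrast; stated power 80% at d = 0.5 and alpha 0.05.

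**Assumptions (not in the article).** A two-sided test; scan-pair loss of 10%, 20% or 30%, equal in both arms; a patient without a usable pair adds essentially nothing to the estimate of the interaction.

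**Step 1: reproduce the stated figure.** For two groups of n, the two-sample t-test has noncentrality d × √(n/2) on 2n − 2 degrees of freedom. With d = 0.5 and n = 30 this is 0.5 × √15 = 1.94, against a critical value of 2.00, and power is 48% (49% by the normal approximation; 61% one-sided). The 80% is not reproduced on that plain reading. It can be reached if d = 0.5 refers to the raw outcome and the correlation r between scans is high:

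- change score: effect = 0.5/√(2(1 − r)); r = 0.77 gives 0.5/√0.46 = 0.737 and 80% power;
- baseline-adjusted analysis: effect = 0.5/√(1 − r²); r of about 0.72 gives about 0.72 and roughly 80% by the normal approximation.

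The article states neither reading, so I do not treat the 80% as wrong here. I grant it and ask what loss does to it.

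**Step 2: grant 80% at 30 complete pairs per arm.** The effect, on the scale of the test, that has 80% power at n = 30 is 0.736, because 0.736 × √15 = 2.85 gives 80% on 58 degrees of freedom.

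**Step 3: remove scan pairs, n = 30 × (1 − loss), effect held at 0.736.**

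| Assumed loss | Pairs per arm | Noncentrality 0.736 × √(n/2) | Power | Effect detectable with 80% power |
|---|---|---|---|---|
| 0% | 30 | 2.85 | 80.0% | 0.74 |
| 10% | 27 | 2.70 | 75.6% | 0.78 |
| 20% | 24 | 2.55 | 70.4% | 0.83 |
| 30% | 21 | 2.38 | 64.3% | 0.89 |

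**Step 4: does this depend on the plain t-test?** The relative loss hardly does. Under the change-score reading with r = 0.77, 80% at 30 pairs becomes 71% at 24 pairs. The absolute detectable effects in the last column do depend on it.

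**Step 5: changes of setting.** Suppose a share c of the high-frequency arm moves to low frequency and gains nothing from the sessions already received. The effect becomes 0.736 × (1 − c). With no scan loss, c = 10% gives 0.662 and 71%; c = 20% gives 0.588 and 61%. These are worst-case values for each assumed share, because they treat every change as if it happened on the first day.

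**The case against.** **A condensed article may leave attrition assumptions to the full protocol.** That is fair, and the absence of a rate is not the point. The point concerns printed figures: a power value is attached to a number, that number equals the number randomised, and the same article lists losses that would reduce it.

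**The power inputs may already carry attrition or non-adherence.** They came from two earlier medication trials whose data are not in the document. If those effects were intent-to-treat estimates, some dilution may be built in. This cannot be excluded. It would not make 30 randomised patients into 30 scan pairs.

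**FIML uses incomplete cases.** It does, and that helps against bias when data are missing at random. With only two scans it does not replace a missing 1-year change.

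**Tempting stronger readings.** A reader might infer that the article claims power for 30 *analysed* patients, or that it forecasts that the planned number will not be reached. It does neither: it speaks of participants, and the passages on missing data and changes of setting are contingency rules without rates. A reader might also conclude that true power is 48%, or some lower figure after loss. Those values rest on a plain two-sample test that the Power calculation section does not state. Nor is analysing switchers as randomised a fault; it is what intent-to-treat requires. The switching figures overstate the dilution for anyone who changes late in the year.

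**Conclusion.** The point holds in a limited form. The direction is secure: the powered number equals the randomised number, no allowance is visible, and any loss of 1-year scans lowers the power of a two-scan interaction test. The stated 80% should be read as an upper limit.

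The size is conditional. Granting the 80% for 30 complete pairs per arm, and assuming equal loss in both arms, 10% to 30% loss leaves about 76% to 64%. At the low end this is modest. Dilution from changes of setting can only add to it, but its amount depends on how many patients change and when, and the documents fix neither. The loss is separate from the question of how 80% was obtained at d = 0.5: a corrected figure for 30 complete pairs would still need this allowance.

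**What to change.** In the Power calculation section:

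1. State that 30 per arm is the number randomised.
2. Restate the power, or the effect detectable with 80% power, for the expected number of patients with two usable scans.
3. Give the assumptions behind it: loss rate, test, sidedness and baseline-to-1-year correlation.
4. Add a sensitivity range for dilution from changes of setting, and label full dilution as the worst case.

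As illustration only, and not as replacement wording, a plain two-sided two-sample t-test can detect d = 0.74 with 30 pairs per arm and d = 0.83 with 24.

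The cost is a short recalculation and a few lines of text. Enrolment, conduct and the planned analysis stay as they are. The only downside is a less favourable stated figure.

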#### Primary outcomes: MRI brain measures

Assessment will comprise the following MRI brain measures. Anatomical MRI: measures of cortical thickness at all points across the cerebrum. Resting State Functional MRI (rsfMRI): measures of functional connectivity throughout the brain. Cyberball Task-Related Functional MRI (fMRI): measures of brain activation throughout the brain in response to trust, mistrust (social exclusion), and rebuilding of trust (social re-inclusion). Diffusion Tensor Imaging (DTI): measures of fractional anisotropy and average diffusion coefficient.

What these outcomes tell us about the brain MRI is an entirely safe way of imaging the brain at any age. It is routinely performed in unsedated people at multiple time points, including multiple time points within an RCT, and without the need for exposure to any radioactivity. MRI scanning can be performed in different modes, with each modality providing unique information probing different aspects of the brain’s structural and functional organization. *Anatomical MRI* provides information about brain structure, most commonly the volumes and shapes of particular brain regions. *Diffusion Tensor Imaging (DTI)* provides information about tissue organization within the brain, especially white matter fibers that connect one brain region to another. At each voxel, Fractional Anisotropy (FA) measures the directional diffusion of water, Mean Diffusivity (MD) measures the overall diffusion of water, Axial Diffusivity (AD) measures diffusion along the long axis of diffusion, which is presumed to be along the long axis of the fiber bundle, and Radial Diffusivity (RD) measures diffusion perpendicular to the long axis of diffusion or fiber bundle. *Functional MRI (fMRI)* provides measures of time-dependent changes in the relative concentration of deoxyhemoglobin within each voxel, which itself is driven largely by changes in oxygen use and the underlying changes in neuronal activity within the voxel [87, 88]. Measures of *resting state connectivity (rsfMRI)* are in essence measures of cross-correlation for the fMRI series of two different voxels (i.e., two different points in the brain), which assesses how strongly those two regions communicate with one another over time.

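### The stated 80% power is set at α = 0.05 per modality, but results count only at FDR-corrected p < 0.05; the power under that rule is not given and is lower for any given location

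*Protocol article*

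**What the plan says.** Under Power calculation, the article plans 30 people in each of three groups and claims that this number "would afford us a power of 80% to detect a moderate-to-large effect size (Cohen d = 0.5) with an α = 0.05 in each imaging modality". The four modalities are anatomical MRI, task-based fMRI, resting-state fMRI and DTI. No correction for multiple testing is mentioned there, and the section does not say whether the 80% refers to a single location, a named region, or any finding in the modality.

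Under Data analysis, the primary comparison is between the two patient arms: "We will test a priori Primary Hypotheses in the 60 depressed participants by assessing a treatment-by-time interaction". Multiple comparisons are corrected by FDR, and "FDR-corrected *p*-values < 0.05 will be color-coded and displayed on a template brain".

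Under Primary outcomes: MRI brain measures, the anatomical outcome is "measures of cortical thickness at all points across the cerebrum". Connectivity and task activation are likewise measured throughout the brain. Two primary hypotheses are more focused: the Cyberball hypothesis names ventral medial regions, and the connectivity hypothesis singles out the default mode network. The cortical-thickness and DTI hypotheses name no region.

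**The concern.** The power statement gives one effect size at one α, which describes a single test per modality. The decision rule is a different one: many locations are tested, and each must pass an FDR-corrected threshold. A figure derived for the first rule does not carry over to the second.

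The MRI measures are the primary outcome, and the power paragraph is the article's only quantitative support for 30 per arm. A reader who takes the 80% as the chance that a truly affected location or region shows up on the map will give too much weight to its absence. The secondary hypothesis on psychopathology also ties clinical improvement to the regional MRI changes that respond to session frequency, so sensitivity at regional level matters beyond the maps.

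**Working it through.** **Inputs from the article.** 30 versus 30 patients, α = 0.05, power 80%, d = 0.5, and a declaration rule of FDR-corrected p < 0.05. **Not in the article, so assumed:** the share π of locations with a true effect (varied from 1% to 90%), equal effects at those locations, a two-sided test, and Benjamini-Hochberg as the FDR procedure.

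**1. The plan's own figure.** For a two-sample t-test on change, df = 58 and the noncentrality is d × √(30/2) = d × √15. At d = 0.5 this is 1.94, and power at two-sided 0.05 is 47.8%, not 80%. The stated 80% is reached if d is expressed on the raw-score SD and the pre-post correlation is about 0.77 (change score) or 0.73 (ANCOVA); neither is stated. That is a separate question. To keep it apart, the steps below start from the effect that does have 80% power at uncorrected 0.05 with 30 versus 30: d = 0.736.

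**2. Direction.** Benjamini-Hochberg's raw p-value cut-off equals 0.05 × (fraction of tests rejected). It is below 0.05 unless every test is rejected. Any location with 80% power at 0.05 therefore has less than 80% under the FDR rule. This needs no assumption about π.

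**3. Size.** With many locations the cut-off t solves

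t = 0.05 × [(1 − π) × t + π × power(t)],

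where power(t) comes from the noncentral t distribution with d = 0.736. For π = 0.10: t = 0.00183 and power(t) = 0.350; check: 0.05 × (0.90 × 0.00183 + 0.10 × 0.350) = 0.00183.

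| Share affected (assumed) | Raw p cut-off | Per-location power |
|---|---|---|
| 1% | 0.00004 | 7% |
| 5% | 0.00062 | 24% |
| 10% | 0.0018 | 35% |
| 20% | 0.0050 | 48% |
| 50% | 0.017 | 65% |
| 90% | 0.034 | 75% |

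A simulation with 4,000 locations in 100 blocks and within-block correlation 0.7 gave 24%, 34% and 47% at shares of 5%, 10% and 20%, so spatial correlation hardly moves the averages.

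**4. Any detection.** In the same correlated simulation, the chance of at least one true detection was 0.83 to 1.00 at d = 0.736 across those three shares.

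**5. Effect needed for 80% per location under FDR.** Setting power(t) = 0.80 gives t = 0.04π / [1 − 0.05(1 − π)], that is 0.0021, 0.0042 and 0.0083 for π = 5%, 10% and 20%. Solving the noncentral t at these cut-offs gives d of about 1.05, 0.99 and 0.93.

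**The case against.** The strongest reply is that the power section speaks of power in each imaging modality, not at each location. If it means the chance of finding something real in the modality, the FDR rule can deliver 80% at d = 0.74, as step 4 shows. This stands as far as it goes: the article does not define its power, so it cannot be said that every reading of the 80% is overstated. But the section does not define power as any detection either, and a single surviving point somewhere would not answer hypotheses about ventral medial regions or the default mode network.

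Second, a reader might infer that power under the written rule simply is 24% to 48%, and that most truly affected regions would be missed. The documents do not support either. Those figures hold only for an assumed share of 5% to 20%; at shares of about 30% and above, per-location power exceeds one half.

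Third, a reader might infer that the FDR family is certainly the whole map. The outcome section says what is measured, not over which set the correction runs, and two hypotheses name target regions. In a narrower family the affected share could be large and the loss modest. Even so, it does not vanish at any share.

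Fourth, the derivation rests on data from prior trials that are not shown, and an article may leave detail to the full protocol. A high pre-post correlation could leave room for a stricter threshold. That is possible, but none is stated, and the α that is printed is 0.05 without correction.

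**Conclusion.** The point holds in a limited form. The printed power belongs to a test at α = 0.05, while the printed decision rule is FDR-corrected p < 0.05 over many locations. For a given location the power under that rule is below 80% at every affected share, for an effect that would have exactly 80% at uncorrected 0.05. The shortfall runs from slight (75% at a 90% share) to severe (7% at a 1% share). It rests on equal effects, Benjamini-Hochberg and a share that the article does not give, so no single figure should be quoted as the trial's power.

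It is not shown that the power for at least one true detection per modality falls short, that most affected regions would be missed, or that the FDR analysis itself is wrong. Nor does the point depend on whether d = 0.5 yields 80% at uncorrected 0.05. Restating d as 0.74 would settle that arithmetic and leave this mismatch in place.

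**What to change.** In Power calculation, say which power is meant: per location, per named region, or at least one true detection in the modality. Then replace the uncorrected α by the criterion in Data analysis and restate the power or the detectable effect under it, giving the assumed share of affected locations and the set of tests over which FDR is applied. If per-location power is meant, a usable form is: with 30 per patient arm and FDR 0.05, 80% power requires d of about 1.05, 0.99 or 0.93 if 5%, 10% or 20% of locations are affected.

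The cost is a re-run of the calculation and a change of wording; for a per-location reading the stated sensitivity becomes less favourable. This point requires no more patients and no change to the analysis rule. Making one regional summary per modality the primary test, with the whole-brain maps as support, would also resolve the mismatch if its power were stated at the α used. That is an optional design choice, and it would need regions to be named for cortical thickness and DTI, where the hypotheses name none.
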